#### Intervention Implementation

At the conclusion of each session, participants and facilitators will evaluate the program content, materials, and delivery. Adherence to the program will be assessed and recorded after each intervention session by the project manager, including information on student participation, the completion of all parts of the individual activities, and the achievement of the aims of each of the sessions.

### Data Analyses

Chi square (categorical variables), ANOVA (normally distributed continuous variables), and Kruskal-Wallis tests (non-parametric variables) will be used to compare baseline characteristics between groups, as well as between those with complete data and those who withdrew or were lost to follow-up. Outcomes will be analysed using general linear models for each of the change outcomes, including the main effects of group and time and the interaction of group and time. Sensitivity analyses will be conducted to determine the effect of missing data. All data analyses will be conducted on the basis of intention to treat principles [33].

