**Methods/design:**

Approximately 400 adolescents (aged 12-17 years) will be recruited through Queensland, Australia public and private schools and randomized to the intervention (n = 200) or 'wait-list' control group (n = 200). The intervention focuses on encouraging supportive sun protective attitudes and beliefs, fostering perceptions of normative support for sun protection behaviour, and increasing perceptions of control/self-efficacy over using sun protection. It will be delivered during three × one hour sessions over a three week period from a trained facilitator during class time. Data will be collected one week pre-intervention (Time 1), and at one week (Time 2) and four weeks (Time 3) post-intervention. Primary outcomes are intentions to sun protect and sun protection behaviour. Secondary outcomes include attitudes toward performing sun protective behaviours (i.e., attitudes), perceptions of normative support to sun protect (i.e., subjective norms, group norms, and image norms), and perceived control over performing sun protective behaviours (i.e., perceived behavioural control).

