## Methods/design

### Study design

The study is a two-armed prospective randomised controlled trial in which approximately 400 male and female adolescents aged 12 to 17 years will be randomised in a 1:1 ratio to the intervention or a wait-listed control group using a computer-generated random number sequence. Participants in both groups will complete assessments at baseline and post-intervention.

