### Study Sample

#### Sample Eligibility Criteria and Recruitment Procedures

Ethics approval was received from the Queensland University of Technology Human Research Ethics Committee (approval number 1100000768). Eligibility criteria will include male and female students aged 12 to 17 years from public and private secondary schools across metropolitan and regional areas of Queensland, Australia.

A convenience sample of schools will be recruited using a maximum variation sampling method to ensure participating schools range in social-demographic status and geographical location. Schools will be approached to participate by the study team using an information package by phone, email and face-to-face discussions. The information package will include a letter to the school principal, background information about the study, questionnaire items, and the participant intervention workbook. Consenting schools will be requested to identify teachers (and their students) that will be accessible to the research team. Active consent will be obtained from both the student participating and their legal guardian. Baseline data will be collected from consenting students by the study team at a time and day specified by the school principal.

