#### Intervention

The intervention will focus on: (i) encouraging supportive sun protective attitudes and beliefs, (ii) fostering perceptions of normative support for sun protection behaviour, and (iii) increasing perceptions of control/self-efficacy over using sun protection. Intervention sessions will be facilitated by trained persons from the Cancer Council Queensland and Queensland University of Technology. Facilitators and Queensland University of Technology research staff will be authorised to deliver the intervention with secondary school students during school hours, and all study staff directly involved with the participants and the running of the intervention will be approved to work with minors (have a current Positive Notice Blue Card). The facilitators and Queensland University of Technology research staff will follow the directions of supervising school staff regarding access to child participants and the location of testing. Testing will take place in an accessible area designated by the school principal or supervising teacher, in proximity to normal classroom activities. As required by the Health and Safety requirements for Queensland schools, the supervising teacher will be aware of the intervention testing circumstances. Assistance will be available from school staff when required. The facilitators and Queensland University of Technology research staff will follow the required procedures for visitors to the school.

The intervention will be delivered during three × one hour sessions over a three week period, and each session will address a different construct. Week one will be designed to encourage supportive sun protection related attitudes and beliefs. Week two will focus on fostering perceptions of friendship group normative support for sun protection. Week three will aim to increase perceptions of control/self-efficacy over using sun protection. Activities for the intervention will include group based discussions, practical sessions on being sun safe (e.g., role playing activities to convince friends to be sun smart), watching relevant sun safety DVDs, setting sun safe goals, and students creating their own internet and/or text message campaigns to encourage sun safety amongst young people. At the conclusion of each session, participants and facilitators will evaluate program content, materials, and delivery.

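### The outcome model has no term for the intervention session groups, so tests of intention and behaviour are anti-conservative if change correlates within those groups

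*Protocol article*

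**What the plan says.** **Allocation.** The Study design section states that "approximately 400 male and female adolescents aged 12 to 17 years will be randomised in a 1:1 ratio to the intervention or a wait-listed control" arm. The unit is the individual student.

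**Model.** The Data Analyses section specifies: "Outcomes will be analysed using general linear models for each of the change outcomes, including the main effects of group and time". The only further term listed is the group-by-time interaction. No school, class, facilitator or session-group term and no cluster-robust variance appears anywhere in the article.

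**Delivery.** The abstract says of the intervention: "It will be delivered during three × one hour sessions over a three week period from a trained facilitator during class time". The Intervention section adds: "Activities for the intervention will include group based discussions, practical sessions on being sun safe", with role play and a week devoted to norms in the friendship group. Under Control, wait-listed students are offered the sessions only once the study is complete.

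**Recruitment.** On schools, the article says: "A convenience sample of schools will be recruited using a maximum variation sampling method". On students within them, it says: "Consenting schools will be requested to identify teachers (and their students) that will be accessible to the research team". The number of schools, class size, number of session groups and session-group size are not given.

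**Sample size.** Alpha 0.05, power 95%, effect size 0.25, 260 completers (130 per group) and 35% attrition, hence 400 recruited. No ICC or design effect is used.

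**The concern.** The model as listed treats every student's outcome as independent of every other's. In the intervention arm that is doubtful by design. Students in one session group share a facilitator, a discussion and one another's influence, and the programme is meant to work partly through peer norms. Some groups may move together more than others. Nothing comparable happens among the controls, so the correlation arises in one arm only (a partially nested design).

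If that correlation is positive, the model understates the variance of the intervention mean, and so of the group and group-by-time contrasts. The nominal 5% test of both primary outcomes then rejects too often, and the effect of a good facilitator or a receptive group can be read as efficacy. The power statement rests on the same independence.

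**Working it through.** **1. The plan's own figure.** Inputs from the Sample size section: alpha 0.05, power 95%, effect size 0.25, 260 completers, 35% attrition. I take the effect size as Cohen's f, since the article calls it medium.
- Noncentral F with λ = f²N = 0.0625 × 260 = 16.25 and 2 numerator df (for example group by time over three time points) gives power 0.957. This matches the stated 95%.
- 260 / (1 − 0.35) = 400, as stated.

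The figure is therefore explained with students treated as fully independent.

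**2. Does recruitment through schools and teachers inflate the error?** Simulation under the null of an unadjusted test, with 260 completers, classes of 20 and individual randomisation. The class effect is shared by both arms.

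| ICC | Simple randomisation | Stratified within class |
|---|---|---|
| 0.02 | 0.051 | 0.046 |
| 0.05 | 0.052 | 0.044 |
| 0.10 | 0.051 | 0.040 |

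It does not. The test is at its nominal level or slightly conservative.

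**3. Does group delivery in one arm inflate the error?** Neither ICC nor group size is in the article, so both are assumed.
- Assume 25 enrolled students per class. Split 1:1, 12.5 go to the intervention and 12.5 × 0.65 = 8.125 complete.
- If session groups pool two such classes, 25 × 0.65 = 16.25 complete.
- Design effect in the intervention arm: D = 1 + (m − 1) × ICC.
- Variance inflation of the difference, with equal arms and clustering in one: I = (D + 1)/2.
- True type I error: 2 × [1 − Φ(1.96/√I)].
- Power at 260 completers: the 2-df calculation of step 1 with λ = 16.25/I.

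| m | ICC | D | I | SE ratio √I | Type I error | Power |
|---|---|---|---|---|---|---|
| 8.125 | 0.02 | 1.143 | 1.071 | 1.04 | 5.8% | 0.94 |
| 8.125 | 0.05 | 1.356 | 1.178 | 1.09 | 7.1% | 0.92 |
| 8.125 | 0.10 | 1.713 | 1.356 | 1.16 | 9.2% | 0.88 |
| 16.25 | 0.02 | 1.305 | 1.153 | 1.07 | 6.8% | 0.93 |
| 16.25 | 0.05 | 1.763 | 1.381 | 1.18 | 9.5% | 0.87 |
| 16.25 | 0.10 | 2.525 | 1.763 | 1.33 | 14.0% | 0.78 |

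The formula was checked by simulation for groups of 20 in the intervention arm only. It gave 6.8%, 10.6% and 16.5% at the three ICCs, against 7.2%, 10.7% and 16.0% by formula.

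**4. Which correlation matters?** Write a student's outcome at time t as fixed terms + u(j) + v(j,t) + error, where u(j) is a stable effect of group j and v(j,t) one that varies over time. In the change from baseline u(j) cancels and v(j,t) remains. The ICC in step 3 is therefore the ICC of change. A simulation with whole classes allocated (16 classes of 16, ICC 0.10, wholly stable class effect) gave a type I error of 0.045 for the unadjusted change test. The sessions start after baseline, so a session-group effect falls into v(j,t).

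The same algebra bears on the remedy. A random intercept that is constant over time absorbs only u(j) and leaves the group-by-time standard error essentially unchanged.

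**The case against.** **Condensed article.** A separate analysis plan may add random terms, and the word introducing the model terms need not be exhaustive. That is fair as to what may exist. But the article does name the model and its fixed terms and powers the trial as if students were independent, and an analyst following it as written would ignore the session groups.

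**Recruitment.** A reader might infer that sampling through schools and teachers makes the standard errors too small. The documents do not support this. Individuals are randomised, and step 2 shows that a shared school or class effect then does no harm.

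**Allocation of whole classes.** Because sessions run in class time, a reader might infer that intact classes are allocated. Under that design the same formula without the halving gives 8.6%, 14% and 22% at m = 16.25. No section states such allocation and the Study design section says otherwise, so these figures do not measure the plan as written.

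**Stable differences between groups.** They cancel from change, so an ICC of outcome level would overstate the problem. This stands, and limits the point to correlation in change.

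**Unknown size.** ICC, group size and number of groups are all absent. This also stands. With correlation near zero the model would do no harm.

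**Conclusion.** The point holds conditionally. As listed, the model gives standard errors and p-values that are too small for intention and behaviour if change correlates within intervention session groups, even under the individual randomisation described. Such correlation is plausible because delivery is in groups and aims at peer norms.

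Over the assumed range of group size and ICC, the real error rate of the 5% test runs from 5.8% to 14%, and power falls from 0.957 to between 0.94 and 0.78. This rests on equal arms, equal total variance in both, clustering in the intervention arm only, a normal reference for the error rate, and the f = 0.25, 2-df reading for power. The article does not fix a single value within that range.

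**What to change.** 1. State the unit of allocation and whether it is within school.
2. Record school, class and session-group identifiers at delivery, since they may not be recoverable later.
3. Replace the general linear model with a partially nested linear mixed model: repeated measures within student, and a random session-group effect in the intervention arm acting on the post-baseline outcomes or on change (a session-group-by-time effect). A time-constant intercept for school or class is not enough.
4. Use Kenward-Roger or Satterthwaite degrees of freedom. With 130 intervention completers there would be only about 130/16.25 = 8 to 130/8.125 = 16 session groups.
5. Include school as a fixed stratum if allocation is within school. If classes or schools are in fact allocated, use cluster and cluster-by-time random effects in both arms.
6. Report the ICC, and state that the 95% power assumes no clustering.

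The cost is analysis wording and a few identifiers in the dataset. Confidence intervals become somewhat wider and the stated power lower. Keeping 95% power under clustering would need more students; the current number can stand if the reduced power is stated openly.

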#### Sample size

A total of 400 participants (200/group) is aimed to be recruited. Based on our previous research in the area [28], it is anticipated that there will be approximately 35% attrition over 4 weeks of follow-up for reasons such as school absence or failure to complete follow-up questionnaires. A total sample of approximately 260 (400-140) completing participants (130/group) is required to detect a medium effect in sun safety behaviour. This sample size was determined by power analysis using the G*Power program [29,30]. Significance level (alpha) was established at 0.05 to avoid a Type 1 error, power (1-beta) was set at 95% to avoid a Type II error, and effect size was determined at .25. Therefore, for a 95% chance of detecting as significant a 4 week difference in sun safe behaviour, approximately 130 participants in each group are needed to complete the study.

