#### Variables

Demographic data collected pre-intervention will include age (in years) and sex (male or female). Data will also be collected on colour of skin before tanning (very fair, fair, olive or brown, Asian, black), colour of skin with repeated exposure to the sun light without protection (go very brown and deeply tanned, get moderately tanned, get mildly or occasionally tanned, get no suntan at all or occasionally get freckled), natural hair colour (black, dark brown, light brown, dark blonde, light blonde, red), eye colour (dark brown, light brown, green, blue), and hours spent in the sun in the past week.

Primary outcome variables will assess the effectiveness of the intervention in improving students' sun protection intentions and behaviour. Secondary outcome variables will assess the effectiveness of the intervention as a means of improving students' attitudes toward performing sun protective behaviours (i.e., attitudes), perceptions of normative support to sun protect (i.e., subjective norms, group norms, and image norms), and perceived control over performing sun protective behaviours (i.e., perceived behavioural control) (Table 1).

**Table 1 T1:** Primary and Secondary Outcome Measures

Domain	Variable	Number of items	SCALE	MEASUREMENT STRATEGIES

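### The outcome models name no baseline adjustment. Adding the baseline value of each outcome would cut the standard error by about 10% to 17%, and the collected demographics would add about 1% to 2%.

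*Protocol article*

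**What the plan says.** The Data Analyses section applies general linear models to the change outcomes, "including the main effects of group and time and the interaction of group and time". No covariate is named and none is ruled out. The same section gives baseline characteristics one use: comparing the two arms, and comparing students with complete data with those lost. It also promises sensitivity analyses for missing data and analysis by intention to treat.

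The Measurement section has the questionnaire completed one week before the intervention starts, so baseline intention and behaviour exist for every enrolled student who completes it. Under Variables, "Demographic data collected pre-intervention will include age (in years) and sex (male or female"; the same paragraph adds "colour of skin before tanning (very fair, fair, olive or brown, Asian, black", tanning response, hair and eye colour, and hours in the sun over the past week. The pre-intervention timing is explicit for age and sex and only implied for the other items.

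The Sample size section expects "approximately 35% attrition over 4 weeks of follow-up" and gives its inputs as "Significance level (alpha) was established at 0.05", "power (1-beta) was set at 95" per cent, and "effect size was determined at .25".

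**The concern.** A change-score analysis, or a group-by-time contrast that includes baseline as one of the time points, uses each student's own baseline but in effect gives it a coefficient of one. Unless the pre-post correlation is very high, that coefficient is too large, and the estimate carries baseline noise that regression on the baseline value would remove. The plan has the data to avoid this and does not say that it will.

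A second, smaller issue is timing. The arms are to be tested against each other at baseline with no stated consequence for the model. If a difference appears, any decision to adjust would be taken after seeing the data. A list fixed in advance removes that discretion.

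The third issue is attrition. With 140 of 400 students expected to be lost, a model that conditions on predictors of both outcome and dropout rests on a weaker missing-at-random assumption than one that does not.

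**Working it through.** **Plan's own figures.** The article states "A total sample of approximately 260 (400-140) completing participants (130/group) is required to detect a medium effect". The dropout step reproduces exactly: 260/(1 − 0.35) = 400. The 260 itself is not reproduced by the variants tried. Reading 0.25 as Cohen's f (the metric is not named; for two groups this is d = 0.5), an F test with one numerator degree of freedom needs 210 in total, and one with two needs 251. Since 260 exceeds both, this does not affect the present point.

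**Inputs for the check.** From the article: 130 completers per arm, alpha 0.05 (taken as two-sided), 95% power. Assumed: d = 0.5 in units of the outcome SD, equal variance before and after, independent students, one follow-up time, pre-post correlation r from 0.4 to 0.6, and a share q of outcome variance explained by the demographic covariates.

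**Step 1: baseline value of the outcome.** With outcome variance 1, the residual variance is 2(1 − r) for a change score and 1 − r² with the baseline value as covariate. The ratio of standard errors is √[(1 − r²)/(2(1 − r))] = √[(1 + r)/2].

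| r | change-score variance | baseline-adjusted variance | SE ratio | SE reduction |
|---|---|---|---|---|
| 0.4 | 1.20 | 0.84 | 0.837 | 16.3% |
| 0.5 | 1.00 | 0.75 | 0.866 | 13.4% |
| 0.6 | 0.80 | 0.64 | 0.894 | 10.6% |

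Simulation agrees to within sampling error, which gives the rounded range of 10% to 17%.

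**Step 2: demographic covariates.** Age, sex and skin colour hardly vary over four weeks. If they predict only the level of the outcome, equally before and after, they cancel from the change score and give no precision gain there. With the baseline outcome in the model, their partial R² is q(1 − r)/[(1 − q)(1 + r)].

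- q = 0.05, r = 0.5: 0.05 × 0.5/(0.95 × 1.5) = 0.018; SE reduction 1 − √(1 − 0.018) = 0.9%.
- q = 0.10, r = 0.5: 0.10 × 0.5/(0.90 × 1.5) = 0.037; SE reduction 1.9%.
- Over r = 0.4 to 0.6 and q = 0.05 to 0.10, the reduction runs from 0.7% to 2.4%.

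A larger gain needs covariates that predict change. If they explained 2% to 10% of the residual variance of the analysed outcome, the SE would fall by 1 − √0.98 = 1.0% to 1 − √0.90 = 5.1%.

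**Step 3: power.** With d = 0.5 and 130 per arm, power = Φ(0.5 × √65/√v − 1.96), where v is the residual variance.

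- Change score: v = 1.2, 1.0 and 0.8 (r = 0.4, 0.5 and 0.6) give 95.7%, 98.1% and 99.5%.
- Baseline-adjusted: v = 0.84, 0.75 and 0.64 give 99.3%, 99.7% and 99.9%.

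The unadjusted change score falls below 95% only when v exceeds 1.25, that is when r is below about 0.375.

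**Step 4: attrition.** Simulation with 200 per arm, about 35% dropout, a true effect of 0.5 SD, and one covariate explaining 5% to 20% of the analysed outcome. Where it drives dropout, it does so with a log-odds slope of 0.5 per SD.

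| How the covariate acts on dropout | unadjusted bias (SD) |
|---|---|
| not at all, or equally in both arms | at most 0.002 in absolute value |
| in one arm only | −0.04 to −0.07 |
| in opposite directions in the two arms | −0.07 to −0.15 |

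Adjusting for the covariate brought the bias to 0.004 SD or less in absolute value throughout.

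**The case against.** The strongest reply is that this is a condensed article. The wording of the model does not exclude covariates, and a covariate list is commonly left to the analysis plan, which is not shown. No stratification factor is described, so no design variable has been omitted, and the unadjusted randomised comparison is valid. All of that stands, and it is why this is an improvement and not an error. It does not remove the point: the article sets out a specific model and gives baseline variables a specific, different role, so the choice of model can be assessed as written.

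A reader might infer that leaving out age, sex, skin type and sun hours sacrifices substantial precision. The documents do not support that. They give no figure for how well these variables predict the outcomes. Variables that predict only level give no precision gain in a change-score model, and about 1% to 2% once the baseline outcome is included. The worthwhile gain comes from the baseline outcome and should not be credited to the demographics.

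A reader might also infer that the plan does nothing about attrition. It does: it compares completers with those lost and plans missing-data sensitivity analyses. The reasons it gives for loss, such as school absence or uncompleted questionnaires, do not indicate dropout that differs by arm. What remains is that the comparison can reveal such a pattern without correcting it, and that sensitivity analyses leave the primary estimate as it is.

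**Conclusion.** The point holds as an optional improvement. The stated model names no baseline adjustment. Regressing on the baseline value of each outcome would lower the standard error by about 10% to 17% relative to a change-score model. That rests on an assumed pre-post correlation of 0.6 to 0.4, equal variances and a single follow-up time. Adding the demographic covariates contributes about 1% to 2% more, assuming that they explain 5% to 10% of the outcome's level.

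The stated 95% power is not at risk over this range under the planned effect read as d = 0.5. Any reduction in attrition bias is conditional on covariates that predict both the outcome and arm-differential dropout. The article neither shows nor excludes this, so the simulated biases illustrate what could happen and do not forecast this trial.

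**What to change.** In the analysis section, replace the change outcome as response by the follow-up value of each outcome. Include the baseline value of that outcome as a covariate, together with pre-specified age, sex, skin type and baseline past-week sun hours, and keep group, follow-up time and their interaction. Report the model without these covariates as a sensitivity analysis, alongside the missing-data sensitivity analyses already planned. State that skin type and sun hours are taken from the pre-intervention questionnaire, and fix the list and the coding of skin type before outcome data are examined. If the analysis plan already contains such a list, a cross-reference is enough.

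The cost is a sentence or two, no new data, and about 4 degrees of freedom out of some 260 completers for the demographic terms if skin type is coded in two groups (1 + 1 + 1 + 1). Keeping all five skin-colour categories would make it 7 (1 + 1 + 4 + 1). The baseline outcome takes one more.

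### The named primary model, a general linear model on change, does not by itself deliver the promised intention-to-treat analysis at the 35% attrition the protocol expects

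*Protocol article*

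**What the plan says.** Three statements in the protocol article bear on this point.

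- **Principle.** The Data Analyses section ends: "All data analyses will be conducted on the basis of intention to treat principles".
- **Model.** The same section analyses the outcomes as change, by general linear models with main effects of group and time and their interaction. Missing data come up in two places only: a comparison of baseline characteristics between students with complete data and those lost, and sensitivity analyses whose method is not named.
- **Expected loss.** The Sample size section says "it is anticipated that there will be approximately 35% attrition over 4 weeks of follow-up", giving school absence and uncompleted questionnaires as reasons. It adds: "A total sample of approximately 260 (400-140) completing participants (130/group) is required".

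The Abstract places the two follow-up assessments at one week (Time 2) and four weeks (Time 3), so an intermediate measurement is already planned.

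**The concern.** A change score does not exist for a student without the follow-up value. A repeated-measures general linear model with a time factor, in its usual form, also deletes listwise: a student with Time 1 and Time 2 data but no Time 3 value leaves the whole model. Nothing in the description of the primary model keeps such students in, although the section claims intention to treat for every analysis.

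With about a third of the sample expected to be lost, this choice matters. If loss depends on how a student responded early on, and does so differently in the two arms, those who remain are no longer comparable by randomisation and the estimated effect is biased. The planned baseline comparison cannot detect loss driven by response after baseline. Sensitivity analyses would help, but they would be read against a primary estimate that may itself be shifted.

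**Working it through.** **1. The plan's own attrition figure.** Inputs from the Sample size section: "A total of 400 participants (200/group) is aimed to be recruited", 35% attrition, 260 completers.

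- 260 / (1 − 0.35) = 400
- 400 × 0.65 = 260, so 140 are lost

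The step reproduces exactly.

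**2. Is power at stake?** The inputs are alpha 0.05, power 95%, and "effect size was determined at .25". The metric is not named. Read as Cohen's f, 0.25 is the conventional medium effect and equals d = 2f = 0.5 for two groups. Read as d, it would need 416 per arm and give only 52% power at 130 per arm, so f is the plausible reading. From the noncentral F distribution with 1 numerator degree of freedom and noncentrality f² × N:

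- N = 260: noncentrality 0.0625 × 260 = 16.25, power 98.0%
- N = 400: noncentrality 0.0625 × 400 = 25, power 99.9%

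Leaving out all 140 would cost about 2 points of power on this calculation. The issue is bias.

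**3. How large could the bias be?** The documents give neither the correlation between assessments nor loss by arm, so these are assumptions:

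- 200 per arm, outcome SD 1, correlation 0.6 between any two assessments, no true effect
- all students seen at Times 1 and 2, and 35% in each arm lost at Time 3
- logit P(lost) = a − b × (Time 2 − Time 1), with a set to give 35% loss; b = 0 means random loss
- completer estimate: difference between arms in mean Time 3 − Time 1 change among those with Time 3, tested at 0.05
- comparison estimate: within each arm, regress change on Time 1 and Time 2 among completers, then average the predictions over all 200 students. It uses the information that a likelihood-based analysis would use when loss depends only on observed data.

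| b, intervention | b, control | Completer bias (SD) | Type I error |
|---|---|---|---|
| 1 | 0 | +0.12 to +0.13 | about 20–22% |
| 0.5 | 0 | +0.07 | about 9–10% |
| 1 | 0.5 | +0.06 | about 8% |
| 1 | 1 | 0.00 | about 5% |
| 0 | 0 | 0.00 | about 5% |

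The ranges come from separate runs. The first row also depends slightly on whether b applies per outcome SD or per SD of the early change. The comparison estimate had bias between 0.000 and 0.002 SD in the two one-arm scenarios.

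Against d = 0.5, the one-arm cases run from 0.07 / 0.5 = 14% to 0.13 / 0.5 = 26% of the target effect.

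**The case against.** The strongest reply is that the article never defines a complete-case set, never excludes students with missing follow-up, and does not say how missing outcomes enter the primary model. A linear model with group, time and their interaction can be fitted to all available records or after imputation. Such detail commonly sits in an analysis plan, which may exist but is not shown. This stands. A reader might infer that the plan is a completer analysis and that the expected 35% will be dropped from the primary result, but the documents do not say so.

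A reader might also take the 260 completers as the intended analysis population. That does not follow. Sizing on completers and dividing by one minus the attrition rate is ordinary practice, including in trials analysed by intention to treat.

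Nor are missing data ignored: the completer comparison and the sensitivity analyses are both planned. Some of the 35% may also have Time 2 data that a suitable fit would use.

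Finally, the larger bias figures come from an assumed difference between arms. No section gives loss by arm, and the stated reasons for loss apply to both. With the same dependence in both arms the null bias disappears, so the upper figures must not be read as a forecast.

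One point survives. The article does more than stay silent: it names a model, and that model in its usual form does not do what the intention-to-treat sentence promises.

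**Conclusion.** The point holds as a mismatch between the named model and the stated principle, not as proof that students will be excluded. In its usual form and without imputation, the model would leave up to 140 of 400 randomised students out of the Time 3 comparison, and would discard Time 2 data from those absent later.

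The consequence depends on why students are lost. Bias is about 0 under the null if loss is random or depends on early response equally in both arms. It is about +0.07 to +0.13 SD, with type I error of about 9% to 22%, if only intervention-arm loss depends on poor early change. These figures rest on the assumed correlation of 0.6, the assumed loss mechanism, and everyone being seen at Time 2. Where students are lost before Time 2, there is less information with which to correct the estimate.

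The change is worth making because it removes this exposure when loss depends only on observed data, and the data it needs are already being collected.

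**What to change.** In Data Analyses, name as the primary analysis a likelihood-based mixed model for repeated measures with group, time and group-by-time terms. Include every randomised student with any available outcome data, in the allocated group. State the assumption it rests on: data are missing at random given arm and the observed outcomes. Multiple imputation using baseline and Time 2 values is an acceptable alternative. Report the completer analysis as secondary. A sensitivity analysis that allows data to be missing not at random is optional.

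The cost is a few sentences of analysis wording and a little programming. No new data, visits or students are needed, and the recruitment target of 400 is unaffected.
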